#### 4.1.2 Spinal cord stimulation proceeding

Spinal cord stimulation (SCS) is a therapy that involves the use of an implantable pulse generator with the potential for enhanced therapeutic success through stimulation algorithms and parameters [28]. By targeting distal areas, such as the dorsal root ganglion, SCS may offer greater anatomical specificity for therapy. Additionally, subthreshold stimulation, utilizing high-frequency or burst energy delivery, has the potential to eliminate noxious and off-target paresthesia. Studies have demonstrated that subthreshold stimulation at high frequencies and/or utilizing different stimulation paradigms can provide equal or even superior pain relief compared with standard SCS [29]. The procedure involves the placement of two octopolar electrodes inserted through the epidural space, positioned beneath the dorsal area posterior to the posterior horn of the spinal cord. The selected level is between the T8 and T11 vertebrae, where the greatest synaptic activity of the spinothalamic tracts responsible for collecting painful sensitivity in the legs and lumbar region is concentrated.

## 5. Patient-reported outcome measures

### 5.1 Primary outcomes

#### 5.1.1 Disability. Oswestry disability index

The Oswestry disability index (ODI) is the most widely used and validated assessment test for lumbar pain. It is a self-assessment test divided into ten sections designed to assess limitations in daily life. Each section has a score ranging from 0 to 5, where 5 was the highest instability level, with the maximum possible score being 50 points [39]. The total rate will be calculated by dividing the participant’s score by the maximum possible score and dividing it by 100 to obtain a percentage [40]. A higher score on the questionnaire indicates greater disability associated with low back pain [41]. ODI is widely regarded as the “gold standard” among tools for assessing functional outcomes in low back conditions [42]. The ODI index is validated to Spanish [43] presenting high sensitivity and specificity to evaluate the function [44,45].

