## 4. Sample size

The sample size will be estimated using GPower® software (Franz Faul, Universität Kiel, Kiel, Germany), version 3.1.9.2. As there are no similar studies allowing for the calculation of sample size based on reference means and standard deviations, a comparison will be made using the difference between two dependent means of 1.95 normal populations, assuming equal standard deviations of 3,2 according to the results obtained from a prior study [37]. Thus, the calculation will be based on the primary outcome of "Disability" and will consider an effect size of 0.70, a power of 0.95 for ANOVA repeated measures, and an alpha error of 0.05. A total of 40 participants (20 subjects per group) will be included in this study. Moreover, considering the probability of loss during follow-up (30%), 12 more participants considering dropout (6 participants per group) will be included, resulting in a total of 52 participants. The possibility of increasing the number of subjects will be explored in case of insufficient statistical power to reach these predefined levels. In the event of dropouts, noncompliance, or absence of results, an intention-to-treat analysis will be conducted.

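### Section 5.1.1 misstates the ODI percentage formula: it divides by 100 where it should multiply, so the scale of the primary outcome is wrong as written

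*Protocol article*

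**What the plan says.** Section 5.1.1 of the protocol article describes the ODI as a ten-section questionnaire. "Each section has a score ranging from 0 to 5", "with the maximum possible score being 50 points". It then converts the total by dividing it "by the maximum possible score and dividing it by 100 to obtain a percentage".

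Section 8.2.2 reports results as mean differences with 95% confidence intervals. It repeats this for the between-group differences from linear mixed models adjusted for baseline. It also plans Cohen's d, and a percent change from baseline in connection with minimal clinically important differences. The analyst takes no part in data collection and receives coded data.

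Section 4 bases the sample size on disability and cites "the difference between two dependent means of 1.95 normal populations, assuming equal standard deviations of 3,2", taken from a prior study. It also says that the calculation "will consider an effect size of 0.70, a power of 0.95 for ANOVA repeated measures, and an alpha error of 0.05". No unit is attached to 1.95 or 3.2.

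**The concern.** A percentage is the score divided by its maximum and then multiplied by 100. The text says to divide both times. The result could never exceed 0.01, which contradicts the sentence's own aim of producing a percentage.

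This is an instruction in the methods, not a background remark, and it governs the only outcome that section 5.1 lists. (The abstract names several primary outcomes, functionality among them, so the claim to sole primary status rests on section 5.1 and on the sample size section.) An analyst kept apart from data collection depends on the written rule. Estimates reported in raw ODI units would be on a scale that no reader could interpret.

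A second, independent gap concerns the same scale. Section 5.1.1 describes both a 0 to 50 total and a percentage, and section 4 does not say whether its planning values are on either.

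**Working it through.** **Inputs.** From section 5.1.1: ten sections, each scored 0 to 5, maximum 50. From section 4: difference 1.95, standard deviation 3.2, power 0.95, alpha 0.05.

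**Step 1: the plan's own maximum.** 10 × 5 = 50. This agrees with the stated maximum.

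**Step 2: the two formulas.** As written: score / 50 / 100. As a percentage: (score / 50) × 100.

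| Raw score | As written | Percentage |
|---|---|---|
| 10 | 0.002 | 20 |
| 25 | 0.005 | 50 |
| 40 | 0.008 | 80 |
| 50 | 0.010 | 100 |

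The ratio is 100 × 100 = 10,000 in every row.

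**Step 3: what the factor changes.** Take raw scores of 25 and 10. Their difference is 50 − 20 = 30 percentage points, but 0.005 − 0.002 = 0.003 under the written rule. Mean differences and both confidence limits shrink by the same 10,000.

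**Step 4: what the factor does not change.**

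- *Tests.* The estimate and its standard error are multiplied by the same constant, so their ratio is unchanged. This also holds in the baseline-adjusted model, because the baseline score carries the same constant.
- *Cohen's d.* The difference and the standard deviation scale together, so d is unchanged.
- *Percent change.* For a fall from raw 40 to raw 25, the percentage scale gives (50 − 80) / 80 × 100 = −37.5%. The written rule gives (0.005 − 0.008) / 0.008 × 100 = −37.5%.
- *Sample size.* 1.95 / 3.2 = 0.609 on any common scale. As a check on invariance only, a comparison of two independent means at 95% power and two-sided alpha 0.05 was run with both values multiplied by 1, 2, 100 and 0.0001. It gave 70 per arm each time. This is not a re-derivation of the plan's 40: the number of measurements and the correlation behind that figure are not stated.

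**Step 5: the unit of 1.95.** On a 0 to 50 score, 1.95 / 50 = 3.9% of the range. On a 0 to 100 score, 1.95 / 100 = 1.95%. The unit affects how the planned difference is read in raw terms. By step 4 it does not affect power or sample size.

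**The case against.** The best defence is that this is a slip that corrects itself. The sentence names its goal as a percentage, and the maximum of 50 is given just before it, so the intended scale can be recovered without any outside source. If the second division is taken to apply to the maximum and not to the quotient, the formula is even right: 25 / (50 / 100) = 50. Nothing suggests that anyone would knowingly analyse an ODI running from 0 to 0.01. An error of that size would be seen at once and could be reversed exactly.

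Most of this stands, and it is why the point is small. It does not make the sentence correct. The more natural reading carries the quotient forward, and a scoring rule with two readings 10,000-fold apart should be rewritten.

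Four stronger readings are tempting, and the document does not support them:

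- *That the error or the missing unit alters the effect the trial is sized for.* Section 4 uses a standardised effect size, and the ratio 0.609 is the same on either scale. (That 0.609 differs from the stated 0.70 is a separate matter.)
- *That the formula leaves the planning values without a usable scale.* The unit is missing from section 4 whatever section 5.1.1 says. Correcting the formula would not supply it.
- *That statements of clinical importance would be on the wrong scale.* The only calculation that section 8.2.2 gives for these is percent change, in which the constant cancels.
- *That 1.95 and 3.2 should be doubled to 3.9 and 6.4.* This assumes that the prior study reported ODI on the 0 to 50 score. The article does not say which instrument or scale that study used.

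**Conclusion.** The scoring formula in section 5.1.1 is wrong as written, by a factor of exactly 10,000 on its literal reading. If it were followed, the raw ODI mean differences and their 95% confidence intervals would be mis-scaled by that factor. Hypothesis tests, Cohen's d, percent change, power and sample size would not be affected. Because the intended 0 to 100 scale can be inferred, this is a wording correction to the primary outcome's definition and not a threat to the design.

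The missing instrument and unit for 1.95 and 3.2 in section 4 is a separate, minor gap. Its only consequence is that a reader cannot place the planned difference on the ODI scale or compare it with an observed mean difference.

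The conclusion assumes that the second division acts on the quotient, and that the same rule would be applied to every ODI score at every visit.

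**What to change.** In section 5.1.1, replace the conversion sentence with: *ODI (%) = (total score / maximum possible score) × 100, range 0 to 100.* Add that all ODI analyses, mean differences and confidence intervals are on this scale.

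In section 4, state which instrument the 1.95 difference and 3.2 standard deviation come from, and in which unit. Give a converted value only after the prior study has been checked.

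The cost is one or two sentences in section 5.1.1 and one in section 4. Nothing changes in the design, sample size, data collection or choice of analysis.

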### 5.2 Secondary outcomes

#### 5.2.1 Quality of life. 36-Item short form health survey

The *36-Item Short Form Health Survey (*SF-36) measures quality of life and comprises several dimensions: (a) physical functioning, (b) role physical, (c) role emotional, (d) social functioning, (e) bodily pain, and (f) vitality, as well as two general dimensions that encompass all the dimensions: a) general health and (b) mental health. The first four subtitles assess the physical health, while the last four assess the mental health [46]. The scale is evaluated between 0 to 100 and high score indicates a better health level, while a low score indicates poor quality of life. It is a widely used instrument in healthcare that highlights the satisfactory psychometric properties of internal consistency and test-retest reliability [47].

#### 5.2.2 Pain perception. Visual analogue scale

The visual analogue scale (VAS, values from 0 to 10) will be used to assess the subjective perception pain (0 will be considered to reflect non-existence of pain and 10 as the worst/intolerable pain). Research personnel will score the paper-based VAS using a ruler to measure the distance (cm) from the left end of the VAS scale to the patients’ marks, obtaining the average VAS value [48]. Previous studies have shown that the VAS scale demonstrated high reliability coefficients (α = 0.98) [49].

### 5.3 Exploratory analysis

#### 5.3.1 Patient’s satisfaction

Patient satisfaction involves the subjective evaluation of treatment effectiveness, health services, and healthcare providers. It represents a complex construct that should not be simplified into a single, one-dimensional item. The Pain Treatment Satisfaction Scale (PTSS) was created to evaluate satisfaction levels among patients experiencing both acute and chronic pain [50]. There are already published studies about diagnosed patients that evaluate their satisfaction using a numeric scale of 11 (-5 to 5) [51,52]. High scores indicate patient satisfaction with the treatment.

#### 5.3.2 Fear of movement. Tampa scale of Kinesiophobia

The TSK will be used to measure fear of movement or reinjury. The TSK is a self-administered questionnaire composed of different questions with a 4-point Likert scale ranging from “strongly disagree” to “strongly agree.” Higher scores indicate greater fear of movement or re-injury, whereas lower scores indicate less fear. The internal consistency of the TSK scores ranged from α = 0.90 with high test-retest reliability {ICC (2,1) = 0.934}[53]. TSK values will be collected following the same data collection protocol.

#### 5.3.3 Self-efficacy

Self-efficacy is a powerful predictor of motivation and learning in people [54]. The self-efficacy questionnaire is composed of 19 items with 3 domains that assess self-efficacy for pain management and physical functioning [55]. These domains analyze limitations in work, social activities, and self-care activities [56]. The Graded Chronic Pain Scale (GCPS) employs 19 questions to identify the chronicity of pain and its impact on the patient [57]. Patients affected by chronic pain may experience it at different sites. This scale addresses pain in general, without classifying it separately [58]. The Spanish version of the Graded Chronic Pain Scale had a high internal consistency (α = 0.87) [59].

#### 5.3.4 Pain catastrophizing scale

The Pain Catastrophizing Scale (PCS), a self-administered questionnaire (13 items on a Likert-type scale from 0 to 4), will be used in this study to assess the level of catastrophizing in the presence of pain [60]. The dimensionality of the scale is characterized by three interrelated factors, which are helplessness, rumination, and magnification, describing a single second-order latent construct (catastrophizing) [61]. The total score ranges from 0 to 52 points, with higher scores representing higher levels of catastrophizing. Studies have reported good levels of content and construct validity, internal consistency, and test-retest reliability for the PCS in examining various musculoskeletal disorders [62,63] and different language versions [64]. In particular, the Spanish version of the PCS has an internal consistency of 0.79 and a test-retest reliability of 0.84 [65]. Low scores indicate low levels of catastrophism and high values show high levels of catastrophism [65,66].

## 6. Program feasibility and safety: Attendance and compliance

There are numerous obstacles and factors that affect the adherence to exercise for individuals with chronic lower back pain [67]. Patients with spine pain are increasingly seeking personalized exercise programs [68]. However, studies have shown that home-based interventions supported by individualized video-based exercise programs result in greater improvement following treatment [69]. The proposed intervention in this study combines these two perspectives. During the initial phases, individualized training will be provided to ensure compliance with the treatment plan and minimize potential complications. Additionally, once the patient begins working from home, the exercises will be accompanied by videos to facilitate daily monitoring of the intervention. Moreover, WHO defines adherence as “the extent to which a person’s behaviour—taking medication, following a diet, and/or executing lifestyle changes—corresponds with the agreed recommendations from a healthcare provider". In the therapeutic exercise group, participants will be encouraged to follow the guidelines at home to complement the intervention. The exercise group should perform the therapeutic exercises according to the instructed regularity as per the SIRAS scale [70].

## 7. Oversight and monitoring

The investigator members ([name] and [name]) who concurred on the study design and applied for funding will comprise the trial steering committee. The principal responsibility of both principal investigators will be to coordinate the execution of the study within the Pain Unit. The remaining participants will actively contribute to the coordination of the patients, application of the treatments, and management of any adverse effects that may arise. In the event of any serious adverse event occurring during the study, the principal investigators will notify the research ethics committee of the “Comité de Ética de la Investigación con medicamentos del Área de Salud de Salamanca” (IBSAL) to take the necessary measures. Furthermore, patients will be contacted by telephone during and after the trial to monitor for any adverse effects.

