The application of integrated interventions may lead to enhanced results in both the short-term and medium-term periods [28]. Combining SCS therapy with physical exercise may not only improve outcomes, but it may also result in a higher number of patients experiencing sustained benefits. However, it is important to consider the potential adverse events that may occur when implementing spinal cord stimulation (SCS) and exercise together, such as electrode migration. Approximately one in ten patients who receive SCS implants experience lead migration [29]. Additionally, the high incidence of lead displacements (3.07%) should not be overlooked [30]. According to the postoperative treatment guidelines, patients are advised to refrain from engaging in any form of exercise or assuming positions that involve the end range of motion in the lumbar spine for a period of two months following the operation. This precautionary measure is necessary as it can potentially result in the migration of the implanted electrode. It is essential to allow sufficient time for the surrounding tissues to undergo fibrosis and securely anchor the electrode in place. Patients with PSPS T2 may have protective attitudes influenced by fear of pain due to movement (kinesiophobia), which can exacerbate patient deconditioning [31]. Therefore, treatment should focus on enhancing the patient’s perceptions and beliefs about movement and addressing not only mechanical and functional parameters but also improving the overall experience [32]. The use of both treatment techniques (SCS/exercise) has resulted in moderate-quality evidence, presenting low-effect measurements when applied in isolation [33]. Furthermore, implementing an exercise protocol that minimizes the risk of adverse effects is crucial. Designing an exercise program based on the range of motion of the spine may be particularly beneficial in avoiding adverse effects on SCS. This study aimed to evaluate the effect of combined treatment with SCS and exercise focused on neuromuscular control of CORE in comparison with isolated treatment with SCS on functionality, pain perception, psychosocial variables, patient satisfaction, adverse effects, and quality of life in patients diagnosed with PSPS-T2. Based on these recommendations, the hypothesis proposed in this study aimed to capitalize on the analgesic effect of posterior cord stimulation during a window of opportunity while the patient underwent re-education through neuromuscular and core control exercises. The integration of these two treatment techniques is expected to yield superior effects compared to the application of a single treatment in isolation.

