### 2.5 Procedure

Once the groups have been established, there will be six sample collections: Pre, Post3weeks, Post2months, Post6months, Post12months and Post18months (Fig 2). Patients will be introduced to the CORE neuromuscular and control motor exercise protocol after surgery.

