	*Iso holds anti extensor facing up*	4	5x5”	7/10	-	120”	Moderate

**Table 2 pone.0309935.t002:** Phase 1 exercise schedule for the second and fourth sessions.

	Sessions 2 and 4						
	Exercise	Series	Repetitions	Intensity	Duration	Break	Effort
**Block 1**	*Hollowing + FB ultrasound*	3	5	4-5/10	-	30”	Low
	*Iso pelvic retroversion + FB stabilizer + hollowing*	3	12–15	4/10	-	30”	Low
	*Bracing + FB ultrasound*	3	5	7-8/10	-	30”	Moderate
**Block 2**	*Iso hip extension push from 90° flexion standing*	4	5x5”	9/10	-	-	Low
	*Bracing + press pallof sitting horizontal with asymmetric feet*	4	8–10	5/10	1,3,2	30”	Low
	*Bracing + press pallof a stride*	4	8–10	5/10	1,3,2	30”	Moderate
**Block 3**	*Monsters walk for medial gluteus guided in parallel*	4	15/side	8/10	1,3,3	30”	Moderate
	*Isotonic clamshell*	4	15–25	9/10	-	-	High
	*Iso holds against rotation facing up in crossed position with hip at 90° and external knees unbalancing + bracing*	4	5x5”	8/10	-	60”	Moderate

*Phase 2A Posture/ alignment*

The second phase of treatment will span from day 16 to day 37 after the intervention. This phase aims to focus on exercises that target the deep spinous-transverse muscles (multifidus), which serve as essential stabilizers for individual spinal segments. As patients have already improved their neuromuscular control during phase 1, the emphasis shifts towards initiating muscle recovery. In this phase, exercises will involve a greater flexion range starting from 65 degrees, similar to phase 1, while the extension range will be extended to 85 degrees. The extension movement of the spine is considered safe as it does not increase neural tension, utilizing the posterior pillar of the facet joints instead. During the 21-day treatment period, patients will attend six monitoring sessions and perform exercises at home safely, following the instructions provided. The exercise progression will be tailored to each patient’s ability based on their pain level. Exercises will be performed from series 1 to 3, with 8 to 15 repetitions, and isometric contractions lasting between 5 and 10 seconds. Breaks between series will last 30 seconds, while breaks between exercises will be 2 to 3 minutes [38].

The exercises for this phase are listed in Tables 3–5.

**Table 3 pone.0309935.t003:** Phase 2A exercise schedule for the first, third and fifth sessions.

	Sessions 1, 3 and 5						
	Exercises	Series	Repetitions	Intensity	Duration	Break	Effort

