#### 8.2.2 Analysis of the outcome measures

Following the Consolidated Standards of Reporting Trials (CONSORT) guidelines on the reporting of RCTs, a per-protocol analysis will be performed. The normality assumption will be checked with the Kolmogorov–Smirnov test and box-plot analysis, while the homogeneity of the variance will be tested through the Levene test. To analyze the acute and short-term effects of SCS and SCS combined with core and control motor exercise on PSPS T2, a two-way ANOVA for repeated measures with experimental groups (i.e., Post3weeks, Post2months, Post6months) as factors will be used, followed by Tukey corrections, to examine time, group, and interaction effects through within- and between-group comparisons (primary and secondary outcomes). The results will be presented as the mean difference (MD) and confidence interval at 95% (IC95%). Effect size (ES) will be estimated by calculating Cohen’s d coefficient. All analyses will be performed using the statistical analysis software SPSS 24 (IBM Inc., Chicago, Illinois, USA). In the case of dropouts during the study or if the statistical power is less than the established 80%, an intention-to-treat principle analysis will be performed [71]. The normality of the data will be tested by visual inspection of histograms, and the characteristics of the participants will be presented using descriptive statistical tests. To assess between-group differences in response to treatment at each post-baseline time point, the mean between-group differences and their associated 95% confidence intervals (CI) will be calculated by constructing mixed linear models using interaction terms (group vs. time). The treatment effects will be adjusted by including baseline outcome values as covariates in the model. Statistical analysis will be conducted by a researcher who is not involved in any of the phases of data collection and will receive data in coded form. Minimal clinically important differences are patient-derived scores that reflect changes in a clinical intervention that are meaningful to the patient. To do this from the delta percentage (Δ%) will calculate using the standard formula: change (%) = [(post-test score − pre-test score)/pre-test score] × 100.

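### Adverse effects are a stated between-arm objective, but no listed outcome measures them, and the planned ascertainment leaves the comparison open to unequal detection

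*Protocol article*

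**What the plan says.** Section 1 (Background) ends with the study aim: to evaluate SCS combined with exercise "in comparison with isolated treatment with SCS on functionality, pain perception, psychosocial variables, patient satisfaction, adverse effects, and quality of life". Adverse effects are one of six named targets. The same section identifies electrode migration as the event to watch when the two treatments are combined. It cites a migration rate of about one in ten implanted patients and a lead displacement rate of 3.07%.

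Section 5 lists the outcomes:
- Primary: ODI.
- Secondary: SF-36 and VAS.
- Exploratory: satisfaction, TSK, self-efficacy and PCS.

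The abstract has its own outcome list, which does not mention adverse effects either. Section 6 is headed "Program feasibility and safety: Attendance and compliance". It deals with adherence, apart from a remark that individual training in the early phases should keep complications low.

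Section 7 gives the only stated routes for adverse events. One is telephone contact: "Furthermore, patients will be contacted by telephone during and after the trial to monitor for any adverse effects". The other is a reporting duty: "In the event of any serious adverse event occurring during the study, the principal investigators will notify the research ethics committee". Neither is limited to one arm.

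Section 2.5 sets a common schedule for both groups: "there will be six sample collections: Pre, Post3weeks, Post2months, Post6months, Post12months and Post18months". Section 8.2.2 uses repeated-measures ANOVA "to examine time, group, and interaction effects through within- and between-group comparisons (primary and secondary outcomes".

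**The concern.** Each of the other targets in the aim (functionality, pain, psychosocial variables, satisfaction, quality of life) corresponds to an instrument in section 5. Adverse effects alone do not. The plan as written therefore poses a between-arm question without a variable or an analysis to answer it, and that question covers the risk the phased limits on spinal movement were built around.

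There is a second, weaker point. If adverse effects are compared anyway, the arms do not have the same opportunity for an event to come to light. Exercise patients meet a physiotherapist repeatedly, and patients on SCS alone have no such sessions. With only a few events expected, one or two noticed in one arm and missed in the other could settle the comparison. A finding of no excess migration, or of excess migration, would then be hard to defend.

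**Working it through.** The document gives no sample size, power or event-rate calculation for safety, so there is no stated figure to reproduce. The check sets sections side by side and then counts contacts and expected events.

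**1. Objective against outcomes and analysis**
- Aim (section 1): adverse effects compared between arms.
- Outcomes (sections 5.1 to 5.3): seven domains, none of them an adverse effect or lead migration.
- ANOVA (section 8.2.2): primary and secondary outcomes, that is ODI, SF-36 and VAS.
- Mixed models (section 8.2.2): no outcomes are named, but the models adjust for the baseline value of the outcome. That suits a score, not a count of post-implant events.

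The objective has no matching outcome or analysis.

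**2. Scheduled post-baseline contacts per arm** (telephone calls cannot be counted)
- Common collections (section 2.5): 6 − 1 = 5 in each arm.
- SCS alone: 5.
- SCS plus exercise, 16 sessions (abstract): 5 + 16 = 21.
- SCS plus exercise, 24 sessions (section 4.1.1): 5 + 24 = 29.
- Ratio: 21/5 = 4.2 to 29/5 = 5.8.

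The two session totals contradict each other and must be reconciled. The point here holds under either.

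In Phase 2A, "patients will attend six monitoring sessions and perform exercises at home safely", and progression depends on the patient's pain level. Symptoms are therefore likely to come up at sessions. That is an inference: no section says adverse events are recorded there.

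**3. Expected events**
- Per arm (section 4 total, 1:1 allocation in section 2.1): 52/2 = 26.
- At about 10% migration: 26 × 0.10 = 2.6 events.
- At 3.07% displacement: 26 × 0.0307 = 0.8 events.

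**4. What zero events would show**
- One-sided 95% upper limit with 0 of 26: 1 − 0.05^(1/26) = 10.9%.
- Two-sided 95% upper limit: 1 − 0.025^(1/26) = 13.2%.

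Even an arm with no migration at all would not exclude the 10% quoted in the background.

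**5. Power, for context**

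With 26 per arm, power is about 17% for 10% against 20%, and about 44% for 10% against 30%. Similar counts would say little about equal safety.

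Steps 3 to 5 concern small numbers and would apply even with perfect ascertainment. They show why missed events matter, not that events will be missed.

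**The case against.** The strongest reply is that the plan sets up no unequal detection. The telephone route reaches patients in both arms, as does notification of serious events. Both arms share six collections up to 18 months, and the evaluating physiotherapist is blinded (section 3). No section makes the exercise sessions a place where adverse events are asked about or recorded. All patients come from one Pain Unit, and their records enter the study system (section 8.1).

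This stands against one tempting inference. A reader might conclude that the safety comparison is biased and that exercise will look more harmful than it is. The document does not support that. Bias depends on the probability of detection in each arm, for which it gives no figure. With equal detection there is no bias, and any numerical distortion would rest entirely on assumed rates.

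A second reply is that a journal article may leave call dates, event definitions and forms to the full protocol, and that the schedule figure (Fig 1), not available here, might list adverse events. This is fair, so the missing call dates are not treated as a fault in themselves. It does not remove the mismatch: the article does set out an outcome hierarchy, and that hierarchy omits one of the targets in its own aim.

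The shared collections and blinded evaluator help less than they might, because neither is stated to include adverse-event ascertainment.

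**Conclusion.** The concern holds in a limited form. The firm part is a contradiction within the article: section 1 makes adverse effects a between-arm target with electrode migration as the named risk, while section 5 defines no such outcome and the ANOVA in section 8.2.2 excludes it. As written, the trial cannot answer that part of its aim.

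The weaker part is exposure to unequal detection: 21 or 29 scheduled post-baseline contacts against 5, if sessions count as contacts. Whether bias would occur, and how large it would be, cannot be determined from the document.

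The expected 2.6 or 0.8 events per arm assume that the background rates apply to this population and that all 26 per arm are followed. Correcting this is advisable because it changes what can be concluded about the trial's main named risk. It does not affect the disability analysis.

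**What to change.** 1. In section 5, add adverse effects as a secondary safety outcome, with lead migration or displacement and lead revision listed separately.
2. Ascertain it with the same structured questions in both arms at the five existing post-baseline collections and at the planned telephone calls, with the calls on the same dates in both arms.
3. Base the between-arm comparison on events found through that common schedule. List events found only at exercise sessions separately, so that they are reported without entering the comparison.
4. In section 8.2.2, state that safety will be reported as per-arm counts with exact confidence intervals, and that similar counts will not be read as evidence of equal safety.

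The cost is protocol wording, a short event form, and slightly longer visits and calls. The collections and calls are already planned, so no new visit is needed. The price in interpretation is a more cautious safety statement.
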